### Data monitoring

This study will be overseen by a study steering committee (SC). The UVESCREEN1 SC will consist of the Chief Investigator, trial staff, and invited members who represent clinical, clinical researcher, and patient stakeholders. The SC will review interim analysis of recruitment figures, adverse and serious adverse events, trial conduct and any substantial amendments to the protocol. The committee will meet 2–3 times a year.

The Chief Investigator will be responsible for the day-to-day monitoring and management of the study. The Chief Investigator will ensure there is adequate monitoring of activities conducted by the study team. This will include adherence to the protocol, procedures for consenting and adequate data quality. The Chief Investigator will inform the Sponsor if there are concerns that have arisen from monitoring activities, and/or if there are problems with oversight/monitoring procedures. Any changes to the protocol including changes to the eligibility criteria, outcomes or analysis will be reported to the study team, sponsor and REC by the chief investigator.

### Ethics considerations and declarations

This study had received ethics approval from Yorkshire & The Humber - Leeds West Research Ethics Committee (REF 23/YH/0237, accepted protocol version V2, date 18/10/2023). The study will be carried out in accordance with the Declaration of Helsinki and all parents of paediatric participants will provide written or electronic informed consent.

### Patient and Public Involvement (PPI)

The development of this study has been supported by a patient expert group, the Childhood Uveitis Study steering group [20,21]. This proposal is also driven by the priorities identified by stakeholders (patients and professional groups) who participated in the 2013 James Lind Alliance Priority Setting Partnership (JLA PSP) [22].

### Dissemination

We estimate participant recruitment to be completed by April 2026 with data collection to be completed by October 2026. Results will be analysed and disseminated approximately six months later. Findings will be disseminated through journal articles and presentations at both academic and medical conferences. Contributors to (i) the design, conduct, data analysis and interpretation (ii) writing (iii) manuscript approval and (iv) accountability for the integrity of the work will, depending on their contribution and journal requirements, will be included by name at the manuscript head. The Uniform Requirements for Manuscripts Submitted to Biomedical Journals (http://www.icmje.org/) will be respected in manuscripts generated by this study. At the end of the trial, after the primary results have been published, the anonymised individual participant data (IPD) and associated documentation (e.g., protocol, statistical analysis plan, annotated blank CRF) will be prepared in order to be shared with external researchers.

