### Study design

This study will be a two-arm, parallel group, single site feasibility randomised controlled trial (RCT) comparing slit lamp examination-based (SLE, routine care) with AS-OCT based detection of active anterior chamber inflammation over 52 weeks in children undergoing surveillance examinations for juvenile idiopathic associated uveitis. Study participants will be children newly diagnosed (within the preceding 12 months) with JIA. The primary outcomes will be study feasibility metrics (i.e., recruitment and attrition rates). Proof of concept analyses will also be undertaken, with comparison of AS-OCT assessment to ‘gold standard’ clinical examination at 6 and 12 months.

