**Fig 1 pone.0316410.g001:**
[figure not shown]
SPIRIT schedule of assessments. ^a^ Visits for those within 6 months of diagnosis: newly diagnosed: Day 1, Week 8, Week 16, Week 28, Week 40, last visit Week 52.Visits for those entering study outside the 6-month widow: Day 1, Week 13, Week 26, Week 39, Week 52.^b^ Concomitant use of a. immunosuppression or immunomodulation (and dose); any eye or visual symptoms since last visit; any other parental concerns.^c^ Measured with age-appropriate method: Cardiff cards, Thomson Kays or Thomson LogMAR in each eye separately.^d^ Heidelberg Spectralis OCT2 and Optovue RTVue anterior segment cube and single line scans.^e^ A diagnosis of new onset uveitis at any visit results in exit from the trial.

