### Analysis

Proportions will be reported as point estimates with 95% confidence intervals. Levels of missing data will be explored with respect to certain baseline characteristics, e.g., age and measures of disease severity to assess biases. All harms or unintended effects in each group will be reported. Initial trial success will be defined as: recruitment rates of > 4 recruits/month, or generation of information on barriers to recruitment; adverse event (incidence of new sight threatening complications in imaging-based surveillance group) rate of 0; adherence to surveillance programme of > 75% or understanding of barriers to adherence. We will seek to identify potential cost drivers to inform the collection of the data for cost-effectiveness analyses within a future definitive study. Within this feasibility trial, effect sizes (of ‘discrimination’ of disease) and variability in outcomes will be estimated with 95% confidence intervals to inform the sample size calculations for a full-scale trial. Efficacy and safety will be analysed according to randomisation group set, which will include all patients who underwent randomisation and who had recorded outcomes (positive detection) during the first 12 months or who completed at least 12 months of surveillance examinations. Missing outcomes (due to attrition) will be considered as an adverse outcome. We will compare the two study arms groups using two-by-two chi-square tests for equality of proportions for disease detection/ adverse outcomes within the OCT arm as compared with the ‘gold standard’ slit lamp examination group.

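### Data collection is stated to end in October 2026, about six months before the last recruits could reach their Week 52 visit

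*Protocol article*

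**What the plan says.** All references are to the protocol article.

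- **Dissemination:** "We estimate participant recruitment to be completed by April 2026 with data collection to be completed by October 2026". Analysis and dissemination follow about six months after that.
- **Study design:** the comparison concerns "detection of active anterior chamber inflammation over 52 weeks".
- **Fig 1 footnote:** children within 6 months of diagnosis attend at "Day 1, Week 8, Week 16, Week 28, Week 40, last visit Week 52"; those entering later after diagnosis attend at "Day 1, Week 13, Week 26, Week 39, Week 52". Both schedules end at Week 52. The only planned early exit, here and in the text under Fig 2, is a diagnosis of uveitis.
- **Study outcome measures:** agreement between AS-OCT and clinical examination is analysed at 6 and 12 months; PedsQL is analysed at 12 months and as change from baseline to 12 months. The Abstract adds the proportion diagnosed with uveitis or other eye disorders at 12 months.
- **Analysis:** the efficacy and safety set takes randomised children with a positive detection in the first 12 months, or "who completed at least 12 months of surveillance examinations". Outcomes missing through attrition count as adverse.

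No section gives late entrants a shorter follow-up or sets a common closing date for all children.

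**The concern.** Both dates come from one sentence, and the interval between them is about half the follow-up that the design requires. If data collection stopped in October 2026, the latest entrants would have no Week 52 visit. Their 12-month data on agreement, uveitis and quality of life would be missing because of the calendar, not because of anything the child or family did.

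The Analysis section then makes the loss depend on outcome. A late entrant with detected uveitis stays in the efficacy and safety set, while a late entrant without it has not completed 12 months and leaves. The section also counts outcomes lost to attrition as adverse, without saying whether calendar truncation is attrition. The same child could be dropped by one reader of the plan and scored as a failure by another. The 12-month estimates are meant to inform the sample size of the full trial, so the ambiguity would carry forward.

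**Working it through.** **Inputs.** End of recruitment: April 2026, day not given, so 1 to 30 April (Dissemination). End of data collection: October 2026, so 1 to 31 October (Dissemination). Follow-up: 52 weeks = 364 days (Study design, Fig 1). Sample size: 80 (Abstract). Recruitment bands: green above 4 per month, yellow 2 to 4, red below 2 (Study outcome measures).

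**Step 1: can October 2026 be reproduced?** End of data collection = last entry + 52 weeks.
- 1 April 2026 + 364 days = 31 March 2027.
- 30 April 2026 + 364 days = 29 April 2027.

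It cannot. The shorter visit schedule does not help, because it also ends at Week 52.

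**Step 2: follow-up available to the last recruit.**

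| Last entry | Data collection ends | Days | Weeks |
|---|---|---|---|
| 30 April | 1 October | 154 | 22.0 |
| 1 April | 1 October | 183 | 26.1 |
| 30 April | 31 October | 184 | 26.3 |
| 1 April | 31 October | 213 | 30.4 |

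Every combination is far short of 52.

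**Step 3: latest entry that can reach Week 52.** End of data collection − 52 weeks is 2 October 2025 for a close on 1 October 2026, and 1 November 2025 for a close on 31 October. The part of recruitment that is too late runs from there to April 2026: 151 to 210 days, or 5.0 to 6.9 months, and about 6 months when like days are matched.

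**Step 4: children affected.** Rate × 6 months, with a steady rate over those months and full enrolment of 80 both assumed:
- 2 per month: 12, and 12/80 = 15%.
- 3 per month: 18, and 18/80 = 22.5%.
- 4 per month, the top of the yellow band: 24, and 24/80 = 30%.

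A rate in the green band gives more than 24. Across the 5.0 to 6.9 month window the count is 9.9 to 13.8 at 2 per month and 19.8 to 27.6 at 4 per month. Children diagnosed with uveitis before the close are subtracted, because their outcome is recorded at exit.

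**Step 5: the 6-month data.** For April 2026 entrants, Week 26 falls between 30 September and 29 October 2026, and Week 28 (the newly diagnosed schedule) between 14 October and 12 November 2026. Only the very last entrants are at risk of losing this visit.

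**Step 6: direction of the selection.** In one arm, let N children enter early enough, with a proportion p detected by 12 months. Let M enter late, with a proportion q detected before the close. Ignoring ordinary dropout, the analysis set holds N + qM children, of whom pN + qM are detected. The excess over p is

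(pN + qM)/(N + qM) − p = qM(1 − p)/(N + qM),

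which is positive whenever any late entrant is detected (and p is below 1). The detection proportion is therefore pushed up. The documents give neither p nor q, so its size cannot be computed.

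**The case against.** The strongest reply is that the dates are a forecast in the Dissemination section, not a rule. Nothing in the design, visit schedule or analysis text tells the team to stop in October 2026. If the team follows the schedule, the report is late and no data are lost. This stands as a limit on the consequence: the loss is conditional on the stated close being applied. It does not reconcile the dates, because both are estimates from the same sentence and the document does not say which governs. Recruitment might also finish well before April 2026. The conflict would vanish if it ended by about October 2025, but the text does not say so.

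Some stronger readings are tempting and are not supported:

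- **A reader might infer that 12-month evaluability is capped at 70%** (24 of 80 lost). The 24 rests on an assumed rate, and late entrants with detected uveitis remain evaluable.
- **A reader might infer that attrition and adverse-outcome rates are certain to be contaminated.** The main feasibility outcome counts loss of consent and loss to follow-up, and the adverse-outcome rule is limited to attrition. A visit that was never due before the close fits neither on a plain reading. Miscounting is possible because truncation is not addressed, but it is not established.
- **A reader might infer that the adherence criterion would fail.** The article does not define adherence as completing Week 52.
- **A reader might infer that the feasibility aims as a whole are undermined.** The eligibility and recruitment proportions and the recruitment-rate criterion are unaffected.

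**Conclusion.** The timeline is wrong as written: about 26 weeks are allowed where 52 are needed, and no choice of days within the stated months closes the gap. If the October 2026 close were applied, uveitis-free children entering after about October 2025 would lose their 12-month agreement, uveitis and PedsQL outcomes. They would also leave the efficacy and safety set on a criterion tied to outcome. That makes it more than a clerical slip.

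The size is about 12 to 24 of 80 children (15% to 30%), less those diagnosed early. It assumes a steady 2 to 4 recruits per month over the last six months and full enrolment; the article gives no start date or monthly projection against which to check this.

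**What to change.** Preferred: define the end of data collection as 52 weeks after the last randomisation, which is about April 2027 if recruitment ends in April 2026. Move analysis and dissemination with it, from about April 2027 to about October 2027. The cost is a report about six months later.

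If October 2026 is fixed: close recruitment by about October 2025. The cost is about six months of recruitment, and possibly a sample below 80.

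If neither is possible: state in the Analysis section that children whose follow-up is cut by the calendar are not counted as attrition, non-adherence or adverse outcomes. Report 12-month outcomes only for children whose Week 52 date falls before the close. That group must be defined by entry date and applied alike to children with and without uveitis, so that inclusion does not depend on outcome. This takes a few sentences and no delay, but it does not recover the 12-month data of the late entrants, and the plan should say so.

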## Discussion

This feasibility, proof-of-concept RCT will compare imaging-based surveillance to routine clinical examination in the detection of uveitis in children at risk, providing the information necessary for the design of a future study. This information will comprise feasibility data needed to finalise eligibility criteria, recruitment and retention approaches, and data to determine the key outcome metrics and study sample size necessary to demonstrate non-inferiority, and the resource use measures needed to determine cost-effectiveness. Study findings are intended to inform the development of a full scale RCT to determine whether imaging-based uveitis surveillance is non-inferior to routine surveillance with regards to detection of childhood anterior uveitis in those at risk. Qualitative interviews will also be completed with selected participants (n = 10) to establish acceptability amongst participants and families and to aid implementation into practice. Longer term impact will be evaluated through the planned full-scale trial.

Attempts to ensure timely diagnosis of childhood uveitis are frustrated by the worsening shortfall in the number of appropriately trained specialists. In some areas of the United Kingdom, children with JIA are not accessing ophthalmic care within the recommended time window [23]. Across the UK, there is a workforce crisis in paediatric ophthalmology [11]. This crisis is replicated globally [24]. The wide community adoption of OCT provides a platform for the use of AS-OCT to address some of these challenges. Specifically, the use of AS-OCT detection of active anterior uveitis would release patients from the need to attend hospital eye specialist clinics, as imaging could be undertaken in community eye health centres. The findings from this proposed research project would support the future implementation of hospital and community based anterior segment imaging-based uveitis surveillance for populations at particular risk but would also be the foundation of future imaging-based surveillance at whole population level. They also provide a chance to put children first, with childhood disease driving the science and implementation, and supporting later wider adoption for adult uveitis. Adult disease is common relative to childhood uveitis (incidence 17–52.4 per 100,000 versus incidence 2–20 per 100,000) [25,26], is a major cause of working age blindness [27] and is the most common cause of attendance to acute eye care services [28].

There are limitations inherent in the design of the proposed study. Firstly, due to the study design, it is not possible for the participants and research team to be masked to the arm to which participants have been allocated, and this may introduce the risk of researcher bias. Equally, due to the nature of the intervention, it is not possible for study participants to be masked to their study arm, which also potentially risks information bias in patient reported outcomes. A pragmatic design, in which each child undertook both standard and interventional examination, with randomisation of which examination would be used for assessment, may be the approach taken for future studies, informed by the findings of this feasibility trial. Secondly, recruitment will only take place at a single site, potentially limiting the generalisability of the data. Additionally, this site is a highly specialised care setting, with participants poorly representative of the ‘average’ patient. Again, as this is a feasibility study, informing a future larger scale study, there will be exploration and description of the representativeness of the recruited patient sample, and reflection of how that compares to what is known about the characteristics of the wider population of children at risk. Participants in this study will be reimbursed for their travel and will consent to regular phone calls to support attendance. As this deviates from routine care, it can be argued that this reduces the generalisability of the study. However, the findings from this study will provide a baseline for best achievable attrition rate to as comparison for the full RCT, where generalisability will be considered again.

In conclusion, this study will provide vital information about the feasibility of conducting a larger scale trial on SLE versus AS-OCT uveitis screening examinations for children with JIA. The data collected in this study will also provide valuable insight into the practical considerations needed before implementing this into a larger scale RCT.

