## Abstract

Children with Juvenile Idiopathic Arthritis (JIA) are at a currently unpredictable risk of a blinding, often asymptomatic, co-existent eye disorder, anterior uveitis which requires prompt treatment. The unpredictability of this insidious disorder commits children with JIA to three-monthly expert clinical examinations in specialist eye centres often located far from their homes. Optical coherence tomography of the ocular anterior segment (AS-OCT) has been shown to be an acceptable, repeatable and sensitive modality for uveitis detection, but is not standard care. This feasibility randomised controlled trial (RCT) aims to inform a future full-scale RCT comparing current routine practice (expert slit lamp examination, SLE) to AS-OCT for the surveillance of uveitis in children at risk. Eighty children aged between 2 and 12 years old and diagnosed with JIA within the preceding year will be included. Participants with an existing diagnosis of uveitis, other ocular co-morbidities or those unable to complete examinations or provide informed assent will be excluded. Participants will be randomised to SLE (control) or AS-OCT (intervention) examination at a frequency consistent with the current national programme for childhood uveitis surveillance. Children in the intervention arm will also have standard examination at 6 and 12 months after study entrance. Outcomes of interest will be feasibility (recruitment and attrition rates), clinical metrics (proportion diagnosed with uveitis or other ocular disorders at 12 months after study entrance), quality of life outcomes (PedsQL), and resource use. Additionally, comparative analysis of AS-OCT versus SLE (‘gold standard’ reference testing) findings at 6 and 12 months for those in the intervention arm will provide the proof-of-concept data necessary to develop and undertake a larger scale trial. Trial registration: This trial has been registered with clinicaltrails.gov (NCT05984758).

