### Study intervention *-* AS-OCT

Children randomised to the intervention arm will undergo AS-OCT imaging to detect anterior chamber inflammation. The AS-OCT images will be acquired using the Optovue RTVue OCT (8 cross-sectional scans) and the Heidelberg Spectralis OCT2 machines (anterior segment cube scan). Images will undergo manual analysis by a trained clinician to identify the presence of inflammatory cells within the anterior chamber. A later semi-automated re-analysis of acquired images will be undertaken within one week of the examination using published protocols [12,14]. Full details of image acquisition and analysis processes are available in supplemental document 1 (S1).

Imaging will be undertaken at a frequency consistent with line with national guidance (Table 1) [9]. This comprises 6 study visits in total (at Month 2 following the first visit to establish eligibility, Month 4, Month 6, Month 9, and Month 12- see Table 1 for further details). The full participant schedule of assessments is shown in Fig 1, with specific details of the study procedures shown in Fig 2.

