**Fig 2 pone.0316410.g002:**
[figure not shown]
Details about the specific procedures during the intervention and control arm. * - See supplemental document 2 (S2) for specific visual acuity screening protocol.

Exit from the study will occur either at visit 7 (for participants with a new diagnosis of JIA within 6 months of entrance to study), at visit 6 (for participants whose JIA was diagnosed within 6 to 12 months of study entrance, Fig 1), or at any visit where uveitis has been diagnosed. A diagnosis of uveitis will be made clinically, using slit lamp examination. Any child within the intervention arm in whom a ‘disease positive’ AS-OCT is acquired (i.e., more than 1 hyper-reflective particle in any cross-sectional scan) will undergo a confirmatory slit lamp examination. Confirmation of uveitis will lead to a child exiting the study.

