### Study outcome measures

The main outcomes of interest are the study feasibility metrics, specifically

- The proportion of patients within the service who meet the eligibility criteria, and reasons for exclusion

- The proportion of eligible patients recruited

- The proportion of patients who withdraw due to loss of consent or are lost to follow-up

- Statistical parameters (point estimates and range/ variance) of the clinical and patient centred outcome measures

The primary clinical outcome measured (as a surrogate endpoint) will be:

- Agreement, for participants in the intervention arm, of AS-OCT findings with routine clinical examination, analysed at 6 months and 12 months milestones

Other clinical outcomes of interest will be:

- New diagnosis of uveitis

- New diagnosis of other visual/ocular problems

We shall be evaluating patient centred outcomes, specifically

- Health related quality of life (PedsQL child self-report, at 12 months and change from

baseline to 12 months)

We shall also be evaluating resource use across the feasibility study to support the design of cost-effectiveness analyses in the larger scale study.

Adverse and serious adverse events (AE/SAE) will be recorded for both the intervention and routine care arms. These events comprise (1) Development of anterior chamber inflammation; (2) development of non-sight threatening sequalae of ocular inflammation during the study period; (3) progression or disease flare of JIA; (4) development of treatment related adverse events. AE/SAE occurring in the intervention arms will be used as criteria to determine progression to a full RCT. Specifically. the progression criteria will be defined using a ‘traffic-light’ system (green – criteria met, amber – minor changes needed, red – significant changes needed).

Recruitment

-Green – > 4 recruits/month-Yellow – 2-4 recruits/month-Red – < 2 recruits/month

Adverse events (incidence of sight threatening complications in imaging-based surveillance group)

-Green/ Yellow – No cases-Red – > 1 case

Adherence to surveillance programme

-Green – > 75%-Yellow – 30-75%-Red – < 30%

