### Randomisation and allocation

Coordinated registration and allocation of participant trial numbers will be used. Participants will be allocated using computer-generated permuted block randomisation into one of two arms (1:1, block size = 4) stratified by age (8 and under, over 8). This will be undertaken centrally by the coordinating trial team using Sealed envelope (www.sealedenvelope.com). Allocation will not be concealed, and participants cannot be masked to their allocation to routine (slit lamp examination) or imaging-based surveillance (AS-OCT) examinations.

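### The text does not keep the slit-lamp and AS-OCT readings at 6 and 12 months independent of each other, so their agreement, the primary clinical outcome, may be inflated

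*Protocol article*

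**What the plan says.** **Outcome.** Under Study outcome measures, the primary clinical outcome, labelled a surrogate endpoint, is: "Agreement, for participants in the intervention arm, of AS-OCT findings with routine clinical examination, analysed at 6 months and 12 months milestones". The Abstract explains how the pairs of results arise: "Children in the intervention arm will also have standard examination at 6 and 12 months after study entrance".

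**Index test.** Under Study intervention - AS-OCT: "Images will undergo manual analysis by a trained clinician to identify the presence of inflammatory cells within the anterior chamber". A second reading follows: "A later semi-automated re-analysis of acquired images will be undertaken within one week of the examination using published protocols". The article does not say whether either reading is masked to the slit-lamp finding, or which of the two enters the agreement analysis.

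**Reference test.** In the text on exit from the study, below Fig 2, uveitis is diagnosed clinically by slit lamp. Any intervention-arm child whose AS-OCT is positive (more than 1 particle in any cross-sectional scan) "will undergo a confirmatory slit lamp examination".

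**Masking.** There are two statements. Randomisation and allocation says: "Allocation will not be concealed, and participants cannot be masked to their allocation". The limitations paragraph of the Discussion says that "it is not possible for the participants and research team to be masked to the arm to which participants have been allocated" and adds that "this may introduce the risk of researcher bias". Both statements are about the arm.

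**The concern.** An agreement figure can be interpreted only if each result is recorded without knowledge of the other. Here both results depend on judgement: a clinician looks for cells on the images, and a clinician looks for cells at the slit lamp. An examiner who knows that the AS-OCT was positive may search longer. A reader who knows that the slit lamp was clear may discount a doubtful particle. Both effects usually push agreement upwards, which here favours AS-OCT.

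The masking that the article discusses is not the masking that this outcome needs. Agreement is measured inside one arm, so knowledge of the arm does no harm to it. Knowledge of the other test's result does.

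The trial is meant to supply proof of concept and to inform the sample size of a non-inferiority trial in children at risk of sight loss. If the two results are recorded with knowledge of each other, no later analysis can separate them.

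**Working it through.** The plan has no figure to reproduce. It states that there is no formal power calculation, and the 95% concordance in Sample size is a starting assumption. The check therefore has two parts.

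**1. What the text fixes about independence**

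| Question | Answer in the article |
|---|---|
| Are both tests due at 6 and 12 months in the intervention arm? | Yes (Abstract, Study design) |
| Is the slit-lamp examiner masked to the AS-OCT result? | Not stated |
| Is the image reader masked to the slit-lamp result? | Not stated |
| Different people, or a fixed order? | Not stated |
| Does a positive AS-OCT lead to a slit lamp? | Yes, for any intervention-arm child, with no milestone exception |
| Which AS-OCT reading is used for agreement? | Not stated |

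Following this text to the letter, a team could read the images, see a positive result, and then perform the milestone slit lamp as the confirmatory one.

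**2. How sensitive the result could be (illustration only)**

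Inputs from the article: 80 children, allocated 1:1, so 80/2 = 40 in the intervention arm before attrition and exits for uveitis; concordance starting point 95%. Assumed inputs, not in the article: agreement *a* under independent readings, and the share *f* of discordant pairs that are reconciled because one result is known.

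Observed agreement = *a* + (1 − *a*) × *f*.

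- *a* = 0.90, *f* = 0.50: 0.90 + 0.10 × 0.50 = 0.95. In children: 36/40 becomes 38/40, so 2 of 4 discordances are reconciled.
- *f* needed to reach 0.95 is (0.95 − *a*)/(1 − *a*): 0.05/0.10 = 0.50 from 90%; 0.10/0.15 = 0.67 from 85%; 0.15/0.20 = 0.75 from 80%.
- Exact 95% confidence intervals: 36/40 gives 76.3% to 97.2%; 38/40 gives 83.1% to 99.4%.
- Binomial chance of observing at least 38/40: 22% if the agreement probability is 0.90, 68% if it is 0.95.

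So two children separate the two results, and the higher from the lower starting value the larger the reconciled share has to be. None of this shows that reconciliation will happen.

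**The case against.** The case on the other side is substantial, and much of it stands.

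- **The limitations sentence is correct.** It concerns the arm. A reader might infer from it that the slit-lamp examiner and the image reader see each other's results. The article does not say so; it leaves masking between tests unstated.
- **The milestone slit lamp is scheduled for every intervention-arm child.** A positive AS-OCT is not what triggers it, and the confirmatory rule matters mainly at visits with no scheduled slit lamp. This stands, but the rule is written without exception and no order is fixed, so knowledge of the AS-OCT result at a milestone is not ruled out.
- **Detail may lie elsewhere.** Fig 2 and supplement S1, which holds the imaging and analysis details, are not shown. If either already masks the readers, one sentence in the article settles the point.
- **There are partial safeguards.** The fixed particle threshold limits discretion on the AS-OCT side, and the semi-automated re-analysis may help if it is masked. Neither protects the slit-lamp side.
- **The size is assumed.** A reader might infer that agreement is inflated and will cross 95%. The article gives no basis for either. The intervals above are wider than the illustrated shift, crossing 95% triggers no decision, and the 95% can also be read as concordance among children with active uveitis rather than overall agreement.

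What remains is that the visible procedure permits a bias that cannot be removed afterwards and is easy to prevent.

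**Conclusion.** The point holds as a risk: agreement **may** be inflated, in the direction that favours AS-OCT, by an amount that the article does not allow anyone to estimate. It rests on the text of the AS-OCT, exit and outcome sections, not on the statement about masking to arm, which is true.

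The movement from 90% to 95% by two children assumes 40 evaluable children at a milestone and half of four discordances reconciled. With fewer evaluable children, each reconciled pair counts for more.

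Severity is moderate. A reader might see a flaw that must be corrected before the trial can proceed. The article does not support that: the main outcomes are feasibility metrics, agreement is called a surrogate endpoint, and the progression criteria are recruitment, adverse events and adherence.

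**What to change.** For the 6- and 12-month visits in the intervention arm:

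1. Complete the scheduled slit-lamp examination and lock it with a time-stamp in REDCap before the AS-OCT images are opened.
2. Then read the images under a coded identifier, without the slit-lamp result.
3. Use that locked slit-lamp record for the agreement outcome. Report separately any slit lamp prompted by a positive AS-OCT. The confirmatory rule itself is unchanged.
4. Keep the manual reading as the index reading, since it appears to be the one that drives surveillance. Putting the semi-automated re-analysis in its place could measure a different test. Report the re-analysis, done on coded images, as a supporting analysis. This matters most if one clinician performs both tests, because a code may not mask that person.
5. In the limitations paragraph, say that the lack of masking concerns the arm and that the two tests are masked to each other at the milestones.

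**Cost.** Protocol wording, a fixed order at two visits and a time-stamped field. No extra examination is needed. A separate image reader would strengthen the design but is not required. The drawbacks are a short delay before images are read at those two visits and a possibly lower agreement figure. If Fig 2 or S1 already fixes the order and masking, a cross-reference is enough.
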